## Abstract

**Background:**

The potential for Bacillus Calmette-Guérin (BCG) vaccination to protect infants against non-mycobacterial disease has been suggested by a randomised controlled trial conducted in low birth-weight infants in West Africa. Trials to confirm these findings in healthy term infants, and in a non-West African setting, have not yet been carried out. In addition, a biological mechanism to explain such heterologous effects of BCG in the neonatal period has not been confirmed. This trial aims to address these issues by evaluating whether BCG non-specifically enhances the innate immune system in term Ugandan neonates, leading to increased protection from a variety of infectious diseases.

**Methods:**

This trial will be an investigator-blinded, randomised controlled trial of 560 Ugandan neonates, comparing those receiving BCG at birth with those receiving BCG at 6 weeks of age. This design allows comparison of outcomes between BCG-vaccinated and -naïve infants until 6 weeks of age, and between early and delayed BCG-vaccinated infants from 6 weeks of age onwards. The primary outcomes of the study will be a panel of innate immune parameters. Secondary outcomes will include clinical illness measures.

**Discussion:**

Investigation of the possible broadly protective effects of neonatal BCG immunisation, and the optimal vaccination timing to produce these effects, could have profound implications for public healthcare policy. Evidence of protection against heterologous pathogens would underscore the importance of prioritising BCG administration in a timely manner for all infants, provide advocacy against the termination of BCG’s use and support novel anti-tuberculous vaccine strategies that would safeguard such beneficial effects.

**Trial registration:**

ISRCTN59683017: registration date: 15 January 2014

**Electronic supplementary material:**

The online version of this article (doi:10.1186/s13063-015-0682-5) contains supplementary material, which is available to authorized users.

## Background

### Background and rationale

Bacillus Calmette-Guérin (BCG) immunisation, the only currently available tuberculosis (TB) vaccine, is one of the most frequently administered immunisations worldwide with more than 100 million children receiving it per year [1]. Although it provides protection against severe forms of TB in children, it has variable efficacy against adult pulmonary disease, with protection generally poor in high-risk areas such as sub-Saharan Africa and Asia [2]. There are currently concerted efforts in the scientific community to improve anti-TB protection either by enhancing existing BCG immunisation strategies or by developing an alternative vaccine [3].

However, it has been suggested that BCG may protect infants against a variety of non-mycobacterial pathogens and thus have beneficial effects beyond protection against TB [4]. The evidence for such a ‘non-specific’ effect of BCG is currently in equipoise. It is, therefore, important and pressing to interrogate this possibility further so that any new vaccine or BCG schedule may be evaluated in terms of overall benefit to recipient, rather than in terms of TB-specific protection alone.

The possibility that BCG may have non-specific beneficial effects on diseases other than TB has been a controversial and highly-debated subject. Observations that BCG may have a greater impact on mortality than can be explained by protection against TB were first made following its introduction more than 80 years ago. Studies including more than 46,500 infants, carried out in the 1940s and 1950s in the USA and UK, showed on average a 25% (95% CI 6 to 41%) reduction in all cause mortality in children receiving BCG compared to those not receiving it [5-9]. This reduction was noted at the time to be larger than could be attributed to the expected reduction in rates of TB. However, as many of these studies were not strictly randomised or controlled, and this was a period of major public health improvements, the results were assumed to result from confounding effects. Similar arguments have been used to dismiss a number of observational studies carried out more recently, in Guinea-Bissau, which appear to show that infants who receive BCG at birth have lower all-cause morbidity and mortality than infants who do not [10-17].

Good quality, randomised controlled trials evaluating the possibility of non-specific effects of BCG are extremely limited. Only one trial has been conducted to specifically evaluate non-tuberculous mortality as a result of altered BCG vaccination schedule [18]. In this trial of low birth-weight infants in Guinea-Bissau, subjects randomised to receive BCG at birth had a 45% lower mortality rate (MRR 0.55 (0.34 to 0.89)) in the first 2 months of life than infants who had BCG immunisation delayed to, on average, 6 weeks of age. The reduction in deaths was due to protection from all-cause febrile illness, respiratory tract infections and diarrhoea, but not against TB (verbal autopsy data). However, although this study is the only trial designed primarily to investigate the impact of BCG on all-cause mortality, nine other randomised controlled trials have been conducted that delayed BCG vaccination past the neonatal period in high mortality areas [19-27]. None of these studies reported significant differences in mortality, either during the period when one intervention group had received BCG and the other group had not, or subsequently. Also, in contrast to the Guinea-Bissau trial, three large cohort studies appear to show that infants who receive BCG vaccination at the same time as Diphtheria Tetanus Pertussis (DTP) vaccination (at 6 weeks of age) have reduced longer-term all-cause mortality than those that have received BCG at birth [28]. Thus, it is currently unclear whether BCG has non-specific beneficial protective effects against diseases other than TB, and if so, what timing of administration would be optimal to induce these effects.

The possibility that BCG may have effects against non-tuberculous disease has also had limited acceptance in the scientific and public health communities due to the lack of a confirmed biological mechanism. Investigations into the hypothesis that BCG immunisation might skew the adaptive immune response from the T-helper type 2 (Th2) dominant environment of early neonatal life, toward a more protective T-helper type 1 (Th1) environment, have been inconclusive [29-32]. The evidence from the Guinea-Bissau randomised controlled trial, however, shows that any putative immunological mechanism would need to be: 1) effective at birth despite the immature neonatal immune system, 2) rapidly inducible (most protection at < 1 week post-immunisation) and 3) active against a range of pathogens. These features would suggest that BCG mediates its non-specific effects by stimulating the innate immune system. This is the hypothesis that we aim to interrogate during this study.

We plan to investigate three different aspects of the innate immune system. Firstly, we will investigate whether non-specific pro-inflammatory cytokine production is enhanced in infants who have received BCG by using *in vitro* stimulation with non-mycobacterial stimulants. Few studies exist investigating alterations in cytokine production to heterologous stimulants following neonatal BCG immunisation [33-35]. The few that have been reported have focused on adaptive cytokines, using a 6-day *in vitro* stimulation protocol, which is sub-optimal for the quantification of innate cytokine production. No studies exist where samples have been collected prior to 5 months of age, thus early non-specific effects of BCG will have been missed. Lastly, *in vitro* stimulants used in previous studies have been antigens (for example, lipopolysaccharide or tetanus toxoid) and not whole organisms, potentially excluding the effect of other important pattern recognition receptor pathways. As part of this proposed study we aim to address these issues by focusing on the impact of BCG on innate cytokine production, conducting overnight stimulation using non-mycobacterial whole organism stimulants, and by using blood samples taken before 10 weeks of age.

Secondly, we will investigate whether BCG might mediate any non-specific beneficial effects by inducing a plasma hypoferraemia. Iron supply is critical for the virulence of most pathogens [36], with plasma hypoferraemia profoundly inhibiting the growth of bacteria [37,38], viruses [39], protozoa [40-43] and fungi [44,45]. As part of the innate acute-phase response, plasma hypoferraemia is induced by IL-6-driven release of hepcidin. Guinea pig models reveal that BCG also induces a rapid bacteriostatic hypoferraemia [46], although involvement of the IL-6/hepcidin pathway has never been studied. To our knowledge, no studies exist investigating the influence of BCG immunisation on the human iron-inflammatory pathway. As part of this study we will investigate whether BCG immunisation in neonates induces alterations to the inflammatory iron axis, as a potential effector mechanism for heterologous protection.

Lastly we will investigate whether BCG induces epigenetic modification at the promoter region of pro-inflammatory cytokines in monocytes, thereby providing a mechanism for ‘training’ the innate immune system to respond in a persistently amplified manner to challenge by non-mycobacterial pathogens. BCG immunisation of naïve adults has been shown to produce trimethylation of histone-3 lysine 4 (H3K4) at the promoter region of TNF-α, IL-1β and IFN-γ in monocytes [47]. This led to enhanced cytokine production following *in vitro* stimulation with the heterologous pathogens *Staphylococcus aureus* (*S. aureus*)*, Streptococcus pneumonia* (*S. pneumoniae*) and *Candida albicans* (*C. albicans*)*,* which persisted to at least 3 months post-immunisation. We will investigate whether BCG immunisation produces similar epigenetic modification of monocytes in neonates.

Thus, we have designed a randomised controlled trial, comparing BCG administration at birth with administration at 6 weeks of age in healthy Ugandan neonates. We will use this to interrogate the impact of BCG vaccination on the innate immune response, as well on all-cause clinical illness outcomes. We believe this study will add significantly to the current debate regarding the non-specific effects of BCG vaccination as it aims to confirm a biological mechanism to explain such effects. Also, by being conducted in healthy neonates, in a geographical location distant from previous studies and by an independent research group, it will help to understand the global applicability of any non-specific effects.

### Aims and objectives

The aims of our study are as follow:To determine whether BCG immunisation at birth alters the innate immune response to heterologous pathogens in the short term (within 1 week)To determine whether BCG immunisation at birth alters the innate immune response to heterologous pathogens in the longer term (at 6 weeks)To determine whether BCG immunisation given at age 6 weeks has similar short- and longer-term effects on the innate immune response to heterologous pathogens compared to BCG immunisation at birthTo obtain data upon the effect of BCG on neonatal susceptibility to invasive infections in Ugandan infants

Aims 1, 2 and 3 will be addressed using sub-studies to interrogate 3 different elements of the innate immune system. The individual objectives for these studies are shown in Table 1. Clinical outcome measures from all 3 sub-studies will be combined to address Aim 4.

**Table 1 Tab1:** **Objectives for immunological sub-studies**

**Sub-study**	**Primary objectives**	**Secondary objectives**
Cytokine sub-study	Cross-sectional comparison of IL-1β, IL-6, TNF-α and IFN-γ cytokine levels following overnight *in-vitro* stimulation with *S. aureus, S. pneumoniae, E. coli, C. albicans* and Poly I:C/CpG between the two intervention groups:	Longitudinal analysis of within-infant changes in innate cytokine production following *in-vitro* stimulation with *S. aureus, S. pneumoniae, E. coli, C. albicans* and Poly I:C/CpG.
	1. Shortly after birth intervention (BCG vaccination/no vaccination): Aim 1	
	2. Six weeks post-birth intervention (immediately prior to first dose of primary vaccination): Aim 2	
	3. Shortly after 6-week intervention (BCG vaccination/no vaccination): Aim 3	
	4. Three weeks post-6-week intervention (immediately prior to second dose of primary vaccinations): Aim 3	
Iron sub-study	Cross-sectional comparison of transferrin saturation and hepcidin levels between the two intervention groups:	Cross-sectional comparison of serum iron, total iron binding capacity, ferritin, transferrin, haemoglobin and red cell parameters at the above time-points.
	1. Shortly after birth intervention (BCG vaccination/no vaccination): Aim 1	Longitudinal analysis of within-infant changes to iron status following *in-vivo* non- specific stimulation (provided by primary vaccinations)
	2. Six weeks post-birth intervention (shortly after first dose of primary vaccination): Aim 2	
	3. Shortly after 6-week intervention (BCG vaccination/no vaccination): Aim 3	
	4. Three weeks post-6-weeks intervention (shortly after second dose of primary vaccination): Aim 3	
Epigenetic sub-study	Cross-sectional comparison of monocyte histone-3 lysine 4 trimethylation (H3K4me3) at the promoter region of pro-inflammatory cytokines between the 2 intervention groups:	Longitudinal analysis of within-infant changes in monocyte epigenetic modification.
	1. Shortly after birth intervention (BCG vaccination/no vaccination): Aim 1	
	2. Six weeks post-birth intervention (immediately prior to first dose of primary vaccination): Aim 2	

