### Study design

This study is an investigator-blinded randomised controlled trial of BCG vaccination given at birth versus BCG vaccination given at 6 weeks of age. Cord blood and two venous blood samples will be collected from participants to allow comparison of innate immune system parameters. All participants will be clinically followed-up until 10 completed weeks of age, to allow comparison of illness outcomes. This study design will allow comparison of outcomes between BCG-naïve and -vaccinated infants up to 6 weeks of age, and early with delayed BCG-vaccinated infants from 6 to 10 weeks of age, helping to identify whether there is a critical period for BCG-induced non-specific effects. The time-point of 6 weeks for the delayed BCG group has been chosen as it is the longest delay possible prior to the potential confounding influence of primary immunisations.

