### Intervention and randomisation

All infants will receive 0.05 ml of BCG-Statens Serum Institute (SSI, Copenhagen, Denmark) (Danish Strain 1331) intra-dermally into the right deltoid. This will be given either at birth (Early intervention arm) or at 6 weeks of age (Delayed intervention arm).

Intervention and blood sampling time-point allocation will be determined by block randomisation, stratified by sex. This will be carried out by an independent statistician, prior to the trial commencement, using Stata (StataCorp, College Station, TX, USA) to generate the allocation sequence. Allocations will be concealed within sequentially numbered, sealed opaque envelopes, prepared by two research assistants who are independent of the trial. Upon delivery of an eligible infant, assignment of allocation will be carried out by midwives who will select the next sequential envelope according to the infant’s gender.

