### Study procedures

#### Overview

Figure 1 shows the SPIRIT (Standard Protocol Items: Recommendations for Interventional Trials) diagram for the trial procedures. On presentation to labour ward, mothers in active labour will be screened for their eligibility and informed consent will be taken. Following delivery the infant will be assessed for eligibility and placental cord blood collected. Infants who are eligible for the study will be randomised as described above, to receive BCG vaccination either immediately or at 6 weeks of age. All infants will be followed-up until 10 completed weeks of age. During this time 2 × 2 ml venous blood samples and 2 stool samples will be collected and all routine immunisations will be given (Oral Polio Vaccination (OPV) at birth and primary immunisations at 6 and 10 weeks of age). Clinical follow-up of the infants will be carried out by weekly telephone interviews to check the well-being of participants, and physician review and anthropometry at each routine clinic visit for blood samples/routine immunisations (on average four visits per participant). Unwell participants presenting to the study clinic or Entebbe Grade B hospital will also be reviewed and managed by the study team, free of charge. Study follow-up is complete once the child has completed 10 weeks of age.

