### Blood samples collected

All participants in the study will have 10 ml placental cord blood collected at birth; divided into 5 ml of heparinised and 5 ml of ethylenediaminetetraacetic acid (EDTA)-anticoagulated blood. They will then have 2-ml venous blood samples collected at 2 time-points between birth and their exit from the study at 10 completed weeks of age. Each sub-study has up to four possible time-points where blood samples are collected, but each infant will only be bled at two of these time-points (randomly allocated) to avoid undue stress for the baby and the mother. The time-points have been selected to enable interrogation of the changes to the innate immune system induced by BCG both acutely following vaccination and in the longer term. The timing of the blood samples in the iron sub-study differs slightly from those in the cytokine and epigenetic sub-studies (see Table 2). These differences are necessitated by the systemic nature of iron metabolism. As hepcidin is produced mainly in the liver this precludes analysis of iron metabolism following *in-vitro* non-specific stimulation. Thus, the iron sub-study will use routine primary immunisations as *in-vivo* non-specific stimuli and measure the resulting changes to iron parameters.

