**Table 2 Tab2:** **Blood sample time-points (T) according to immunological sub-study**

	**Blood sample T1 (first week of life)**	**Blood T2 (6 weeks of age)**	**Blood sample T3 (6 weeks of age)**	**Blood sample T4 (10 weeks of age)**
Cytokine sub-study	5 days after birth	Immediately before primary immunisations	5 days after primary immunisations	Immediately before primary immunisations
Iron sub-study	5 days after birth	1 day after primary immunisations	5 days after primary immunisations	1 day after primary immunisations
Epigenetic sub-study	5 days after birth	Immediately before primary immunisations		

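### Iron T2 is assigned to Aim 2 but is drawn a day after the 6-week primaries, when delayed-arm infants have probably just had BCG

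*Protocol article*

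**What the plan says.** Aim 2, under Aims and objectives, asks whether BCG at birth "alters the innate immune response to heterologous pathogens in the longer term (at 6 weeks". The Study design section says the design compares vaccinated with BCG-naive infants up to 6 weeks of age, and early with delayed vaccination after that.

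In the cytokine and epigenetic sub-studies, T2 is drawn just before the first primaries. In the iron sub-study, Table 1 defines T2 as "Six weeks post-birth intervention (shortly after first dose of primary vaccination): Aim 2" and Table 2 puts it "1 day after primary immunisations". The section on blood samples explains the difference: iron metabolism cannot be stimulated in vitro, so the primaries serve as in-vivo "non-specific stimuli and measure the resulting changes to iron parameters".

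On BCG timing, Intervention and randomisation says: "This will be given either at birth (Early intervention arm) or at 6 weeks of age (Delayed intervention arm". The Overview schedules "primary immunisations at 6 and 10 weeks of age". The Study design section justifies 6 weeks because "it is the longest delay possible prior to the potential confounding influence of primary immunisations".

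**The concern.** Delayed BCG and the first primaries share one nominal age, and iron T2 comes a day later. If BCG is given with or before the primaries, the delayed arm is no longer BCG-naive at iron T2. The in-vivo stimulus then differs by arm: primaries alone in the early arm, primaries plus fresh BCG in the delayed arm. Randomisation does not remove this, because allocation itself creates the difference.

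Both iron primary outcomes, transferrin saturation and hepcidin, are read at this time-point. The sub-study's own hypothesis is that BCG lowers plasma iron. If it does so within a day, the delayed arm's values would fall too, and a lasting effect of birth BCG would be harder to see. A null result could then mean either no lasting effect or two effects offsetting each other.

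**Working it through.** **Inputs.** Delayed BCG at 6 weeks (Intervention and randomisation) and first primaries at 6 weeks (Overview): nominal day 6 × 7 = 42 for both. Iron T2 one day after the primaries (Table 2): 42 + 1 = day 43. Iron T3 five days after them (Table 2): 42 + 5 = day 47. Iron recruitment: 60 per group per time-point, 240 in total (Sample size considerations).

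**The plan's own figure.** 60 infants × 2 groups × 4 time-points ÷ 2 bleeds per infant = 240. This reproduces, and no sample-size figure is in dispute.

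**Order A: BCG with the primaries, day 42.** T2 falls 43 − 42 = 1 day after delayed-arm BCG. T3 falls 47 − 42 = 5 days after it.

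**Order B: BCG held until after the T2 draw, day 43.** The delayed arm is BCG-naive at T2. T3 falls 47 − 43 = 4 days after BCG.

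**Which order does the text favour?**

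- *For A:* the rationale in the Study design section places BCG ahead of the primaries' influence; order B puts it after them.
- *For A:* Table 2 times T3 from the primaries, while Table 1 describes it as soon after the 6-week intervention. Under A, T3 is 5 days after BCG, matching T1 at 5 days after birth.
- *For A:* the Overview describes "physician review and anthropometry at each routine clinic visit for blood samples/routine immunisations (on average four visits per participant" and mentions no separate BCG visit. An infant bled at T3 but not T2 would then have only the immunisation visit for BCG before T3. No different order is given for infants bled at T2.
- *For B:* Table 1 dates T2 from the birth intervention and only T3 from the 6-week one.
- *For B:* the Primary outcomes section classes the 6-week sample as remote from vaccination.

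Order A fits more of the visible text, but neither order is stated.

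**Is recent BCG addressed elsewhere?** Study limitations discusses more recent BCG in the delayed arm only for the 10-week comparison, and expects any bystander effect to have gone after about four weeks. That does not cover a one-day gap.

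**How many infants?** Up to 60 delayed-arm infants at iron T2. The delayed arm has 560 ÷ 2 = 280 infants, so 60 ÷ 280 = 21% of it. Under order B, infants with both T2 and T3 would have T3 at 4 days. If the six possible time-point pairs are used equally (an assumption), that is 120 ÷ 6 = 20 delayed-arm infants; the possible range is 0 to 60.

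**The case against.** The strongest reply is that everything turns on an order that cannot be seen. The schedule is in a figure that is not shown, and a full protocol or operating procedure would normally settle the sequence. A shared age of 6 weeks fixes neither day nor order; the Study design sentence explains a choice of delay and is not an administration instruction. T3 is soon after BCG at either 4 or 5 days. The visit description concerns physician review and may not list every vaccination contact. Order B also makes the Table 1 and Primary outcomes labels correct.

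This stands to the extent that the point must be conditional. A reader might infer that the protocol definitely vaccinates the delayed arm before iron T2; the documents do not support that. They do not show the opposite either: no visible text holds BCG back, and doing so sits badly with the stated rationale for 6 weeks.

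A reader might also infer a known bias or loss of power. That is unsupported. The Background cites a rapid effect in guinea pigs without giving a time, and knows of no human studies. No standard deviation for transferrin saturation is stated. Any power figure would rest on chosen inputs and should carry no weight.

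Nor is Aim 2 lost as a whole. The cytokine and epigenetic T2 samples precede the primaries, and iron T2 remains a valid randomised comparison of the two schedules. Only its interpretation is at issue.

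**Conclusion.** The point holds conditionally, with medium confidence. If delayed-arm BCG is given at or before the 6-week primaries, as the visible text suggests, iron T2 does not supply the vaccinated-versus-naive contrast to which Table 1 assigns it. It compares early with just-given BCG, both in the presence of primaries. One time-point of one sub-study is affected: up to 60 delayed-arm infants and both iron primary outcomes. The size of any distortion is unknown. It would work against finding a lasting effect only if BCG alters iron within about a day, which the documents hypothesise in general terms but do not establish. This should be fixed because it determines what the trial can conclude about iron under Aim 2.

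**What to change.** If BCG is already held until after the iron T2 draw, one sentence in Intervention and randomisation and a note to Table 2 are enough.

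Otherwise:

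1. Record the BCG and bleed times for every infant with an iron T2 sample. Where delayed-arm BCG came first, report the result as early versus just-given BCG, both with primaries, and not as an Aim 2 vaccinated-versus-naive finding. This is cheap.
2. For delayed-arm infants allocated to iron T2 and not yet 6 weeks old, give BCG immediately after the draw at the existing day-1 visit where feasible, or at the next contact if that visit is missed. At the reported status in March 2015, 560 − 240 = 320 infants were still to be recruited, so an early change would reach many of them.
3. If the order changes mid-trial, draw both arms of the Aim 2 contrast from the same recruitment period, so that the comparison stays randomised.

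The second step needs no extra visit but has real costs. BCG comes a day later and after the primaries, a small departure from the stated rationale. BCG timing in the delayed arm comes to depend on bleed allocation and on attendance at the day-1 visit. T3 falls about 4 days after BCG for infants with both bleeds, still within the one-week window in Primary outcomes. A protocol amendment with ethics approval is needed.
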